
## Protocol

### Objectives

The primary endpoint of this Italian nationwide study is to analyze the clinicopathological findings, management strategies and short-term outcomes of gastrointestinal emergency procedures performed in patients over 18. Secondary endpoints will be to evaluate to analyze the prognostic role of existing risk-scores to define the most suitable scoring system for gastro-intestinal surgical emergency. We will conduct an epidemiological investigation to gather information about the number of patients operated on yearly, and the prevalence of various pathological conditions leading patients to need emergency surgery. Furthermore, we aim to identify any specific parameters that may be used as variables for new scoring system, peri-operative variables predicting adverse results and any critical issues in the management of these patients.

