### Outcome measures

The primary outcomes are 30-day overall postoperative morbidity and mortality rates. Secondary outcomes are 30-day postoperative morbidity and mortality rates, stratified for each procedure or cause of intervention, length of hospital stay, admission and length of stay in ICU, and place of discharge (home or rehabilitation or care facility). Severity of every disease will be assessed according to the AAST EGS score (29). Other secondary outcomes include the number of elderly subjects undergoing yearly emergency surgery, reported as the elderly to non-elderly patient ratio, emergency surgery in the elderly per 100,000 inhabitants, frequency of use of frailty score. Elderly are define as any patient >65 years old according to the World Health Organization. Moreover, the study will evaluate the sensitivity and specificity of the following scores: Charlson Age Comorbidity Index (CACI), Simplified Acute Physiology Score II (SAPSII), American College of Surgeons National Surgical Quality Improvement Program (ACS NSQIP), Calculation of Postoperative Risk in Emergency Surgery (CORES), Surgical Mortality Probability Model (SMPM), Urgent Surgery Elderly Mortality (USEM) score, Emergency Surgery Frailty index (EmSFI), 5 modified Frailty Index (5-mFI). The postoperative complications are reported and categorized according to the Clavien-Dindo classification system. Morbidity we will be assessed by detecting all adverse event according “Common terminology criteria for adverse events version 5” (30). Therefore, the Comprehensive Complication Index will be calculated (31).

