### Statistical analysis

The report of this study will be prepared in accordance with guidelines set by the STROBE (Strengthening the Reporting of Observational Studies in Epidemiology) statement for observational studies (30). Statistical analysis will be performed either with SPSS software, version 21 to 26 (IBM Corp. Released 2020. IBM SPSS Statistics for MacOsx, Version 27.0. Armonk, NY: IBM Corp) for MacOSX or StataCorp2019 STATA Statistical Software: release 16 (College Station,TX: StataCorp LLC). First, data normality will be tested using the Shapiro–Wilk test or Kolmogorov– Smirnov test. Dichotomous data and counts will be presented in frequencies. Continuous data will be presented as mean values plus standard deviations, or as median values and interquartile ranges. The 95% confidence interval will always be reported where appropriate. Differences between means will be compared using the independent sample Student's *t* test, the pairwise comparison Student's *t* test, the Mann–Whitney *U* test, the Kruskal–Wallis test or other analysis of variance (ANOVA) tests. Differences between medians will be compared using the Kolmogorov–Smirnov test or special application of the Pearson chi square test by using the median as cut-off. To compare differences in frequencies, Fisher's exact test or *χ*^2^ test, with or without Yates correction will be performed. Receiver operating characteristic (ROC) curve analysis will be performed to estimate sensitivity and specificity of each score. Linear correlation will be assessed by Pearson's or Spearman's test, if needed. Multivariate analyses will be performed using logistic regression models that consider mortality and morbidity as dependent variables. A *P* value of <0.05 will be considered statistically significant.

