### Expected results

We expect to obtain the following results:
•Identification of the mortality rate at 30 days (30-day mortality rate), divided according to the different type of intervention (ICD-9-CM classification) and stratified for 5-years age group;•Identification of the general morbidity index at 30 days (30-day morbidity rate), divided according to the different type of intervention (ICD-9-CM classification) and stratified for 10-years age group;•Identification of mean length of hospital stay (LOS), in days, according to the different surgical procedure group (ICD-9-CM classification);•Sensitivity and specificity of the following scores:
- Charlson Age Comorbidity Index (CACI)- Cohomprensive Complication Index- Simplified Acute Physiology Score II (SAPSII)- American College of Surgeons National Surgical Quality Improvement Program (ACS NSQIP)surgical risk calculator- Calculation of postOperative Risk in Emergency Surgery (CORES)- Surgical Mortality Probability Model (SMPM)•Evaluation of the prevalence of emergency surgery in different age groups by geographic area (Emergency surgery per 100.000 inhabitants);•Identification of an Elderly / Non Elderly ratio;•Evaluation of the use of the following scores in elderly patients:
- Frailty Fried Index- Canadian Study of Health and Aging (CSHA) frailty score- Emergency Surgery Frailty Index (EmSFI)- Urgent Surgery Elderly Mortality (USEM) score- 5 modified Frailty Index (5-mFI)

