## Discussion

Emergency gastrointestinal surgery (EGS) is challenging in terms of decision-making, managing co-morbidity and post-operative rehabilitation with substatntial morbidity and mortality rate (31). On the light of this, it is pivotal to define the possible clinical-pathological features, pathways and treatment for gastrointestinal emergency (GE). Moreover, approximately half of all patients undergoing EGS will develop a postoperative complication, and up to 15% will be readmitted to the hospital within 30 days of their surgery (32). More recent pathophysiology knowledges and together with improved surgical and anaesthesiologic techniques allowed the surgeon to achieve better results in treating these high-risk patients (33, 34). However, diagnosis and treatment of GE still remain a challenge. In patients with GE, early warning scores (EWS) associated with abdominal signs and symptoms such as abdominal pain and tenderness can screen for patients needing prompt surgical procedures (35). EWS employ physiological, easy-to measure parameters, assessing variables such as systolic blood pressure, pulse rate, respiratory rate, temperature, oxygen saturations, and level of consciousness (36–39). However, physiological parameters are often not sufficient for risk stratification, as the GE involves a wide range of patients of different ages, with different disease, different morbidities and therefore different functional reserves. In the light of this, conceding the clinical importance of GE, considerable research is directed at identifying biomarkers suitable in predicting the severity and outcomes. Starting from previous researches, we have undertaken this project particularly focusing on reporting which are the EGS procedures that account for the greatest number of cases, deaths, complications, and inpatient cost; on the age-related and disease-related clinical differences as independent risk factor for the main clinical course; on the sensitivity and specificity of actual score in predicting EGS outcomes.

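### The existing risk scores are to be judged by ROC sensitivity and specificity alone, which cannot show whether tools that predict a probability give the right absolute risk

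*Protocol article*

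**What the plan says.** The Objectives section of the protocol article sets a secondary aim: "to analyze the prognostic role of existing risk-scores to define the most suitable scoring system for gastro-intestinal surgical emergency". Four sections then name how the scores will be assessed, always in the same terms:

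- Outcome measures: "the study will evaluate the sensitivity and specificity of the following scores", followed by eight tools (CACI, SAPSII, ACS NSQIP, CORES, SMPM, USEM, EmSFI, 5-mFI).
- Statistical analysis: "Receiver operating characteristic (ROC) curve analysis will be performed to estimate sensitivity and specificity of each score".
- Expected results: "Sensitivity and specificity of the following scores".
- Discussion: the project will focus, among other things, "on the sensitivity and specificity of actual score in predicting EGS outcomes".

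No section mentions calibration, observed against expected deaths, goodness of fit or a Brier score. None gives a cut-off for any score. The Statistical analysis section also plans regression: "Multivariate analyses will be performed using logistic regression models that consider mortality and morbidity as dependent variables". It does not tie these models to the risks that the existing scores predict.

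On intended use, the Introduction looks for tools to support the surgeon's decisions, and the Conclusion hopes to spare patients treatment that would be futile.

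**The concern.** Sensitivity and specificity from a ROC curve describe discrimination: whether patients who die tend to score higher than those who survive. They do not say whether a predicted risk of 20% corresponds to about 20 deaths per 100 such patients. Decisions about high-risk or possibly futile surgery depend on that second property.

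At least two of the listed tools output a risk, judging by their names. One is the "Surgical Mortality Probability Model (SMPM"); the other is the ACS NSQIP tool, which Expected results calls a surgical risk calculator. CORES may be a third. When an existing tool is moved to a new population, its absolute risks may be systematically too high or too low. The named measure could not reveal this, so a badly calibrated tool could be recommended as the most suitable one.

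**Working it through.** **Figures in the document.** It states no sample size, expected mortality, expected AUC or cut-off, so there is no figure of its own to reproduce. The inputs below are assumptions, shown over a range.

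**Step 1: the ROC curve does not change (no assumption needed).** Let p be the true risk and let a miscalibrated tool double every odds:

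q = 2·[p/(1−p)] / (1 + 2·[p/(1−p)]) = 2p/(1+p).

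This is strictly increasing in p, so every pair of patients keeps its order. The ROC curve and AUC are identical for p and q. For single patients:

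- p = 5%: 0.10/1.05 = 9.5%
- p = 10%: 0.20/1.10 = 18.2%
- p = 20%: 0.40/1.20 = 33.3%

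**Step 2: effect on the average prediction.** Assume logit(p) is normal across patients, with its mean set to give the stated mortality. O/E is observed mortality divided by mean predicted mortality and equals 1 for a calibrated tool. Simulation with 400,000 patients, SD 1.5 on the logit scale:

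| Assumed mortality | AUC, correct tool | AUC, odds doubled | Mean predicted, odds doubled | O/E |
|---|---|---|---|---|
| 3% | 0.841 | 0.841 | 5.4% | 0.56 |
| 5% | 0.840 | 0.840 | 8.6% | 0.59 |
| 10% | 0.832 | 0.832 | 16.1% | 0.62 |
| 15% | 0.826 | 0.826 | 23.0% | 0.65 |

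In the 5% row the simulated sample had 5.07% deaths, so O/E = 5.07/8.63 = 0.59. With exactly 5.0% it is 5.0/8.63 = 0.58.

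With SD 1.2 and 5% mortality, the AUC is about 0.79 for both tools, mean predicted mortality is 8.9%, and O/E = 5.0/8.9 = 0.56. The share of patients labelled at 20% risk or more rises from 3.6% to about 11%. Halving the odds instead gives O/E of about 1.9 with the same AUC.

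**Step 3: what a ranking-based choice would do.** At 5% mortality and SD 1.5, a rival that ranks patients slightly less well has AUC 0.826. It would lose to the doubled-odds tool at 0.840, even if the rival's absolute risks were right.

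**Step 4: when sensitivity and specificity would react.** At the cut-off that maximises their sum, both tools give 0.787/0.731 (5% mortality, SD 1.5); only the cut-off moves, from 4.6% to 8.8% predicted risk. At a cut-off fixed beforehand at 10% predicted risk, the pair changes from 0.570/0.888 to 0.752/0.764. The distortion is therefore hidden when the whole curve or a data-derived cut-off is used, and visible at a fixed absolute-risk cut-off. The document fixes none.

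**Step 5: what calibration measures would show.** Doubling the odds adds ln 2 = 0.69 to every predicted logit. The calibration intercept would be −0.69 with slope 1, alongside the O/E values above. The slope alone would miss this error, so the intercept and O/E are needed too.

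**The case against.** The strongest reply is that this is a condensed article and that calibration plots, cut-off rules and optimism correction are usual content of an analysis plan that is not shown. For cut-offs this stands: their absence here is not a fault in itself. It does not stand for the performance measure, because the article states that choice in four sections. An analysis plan that follows the text would assess discrimination only.

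A second reply is that sensitivity and specificity are not blind to wrong risks in general. That is right, as Step 4 shows; the point holds for the ROC curve as a whole and wherever no absolute-risk cut-off is fixed.

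A third is that most of the listed tools are not named as probabilities and that discrimination is a reasonable common yardstick. That limits the scope. The doubled-odds example does not apply to points until they are mapped to a risk. Discrimination should stay, but not as the sole measure.

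A reader might also infer that cut-offs will be picked on the study data, so that the reported sensitivity and specificity will be too favourable. The document does not say so: a ROC analysis can equally be read at a published cut-off. Such optimism would also depend on event numbers that the document does not give. Nor does the document state a rule by which a particular miscalibrated score would win; the loss in Step 3 assumes a choice by AUC.

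**Conclusion.** The point holds in limited form. The stated measure cannot detect wrong absolute risks in tools that predict a probability, although the aim is to name the most suitable score and the hoped-for use involves judging futility. That the ROC curve is unchanged is a mathematical fact. The illustrated size, O/E of about 0.56 to 0.59 with odds doubled at 5% mortality, rests on an assumed mortality, an assumed spread of risk and an assumed degree of miscalibration. It does not show that any listed score is miscalibrated in this population.

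The scope is SMPM and the ACS NSQIP calculator, judging by their names, and possibly CORES. This is a secondary aim, and the primary outcomes of 30-day morbidity and mortality are untouched. The change should be made, because as written the choice of a most suitable score would rest on ranking alone.

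**What to change.** In the Statistical analysis section:

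1. For each tool that outputs a probability, add the observed/expected ratio, calibration intercept and slope, and a calibration plot, with 95% confidence intervals. Do this for 30-day mortality, and for morbidity where the tool predicts it.
2. For points-only scores, report observed mortality per score band with 95% confidence intervals.
3. State that both calibration and discrimination will be considered in naming the most suitable score.

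As a secondary recommendation, report sensitivity and specificity at the published cut-off where one exists, and correct for optimism if a cut-off is derived from the study data.

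The cost is a little extra analysis and one check. The Score row of Table 1 lists the tools by name without saying whether points or predicted risks are recorded. The sponsor should confirm that predicted risks are stored, or that they can be computed from the variables collected. A reader might assume that the forms need no change, but the document does not establish this.

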### Study design and participating sites

The prospective, observational study will be conducted following a resident-led model, similar to what has been described by Banghu et al. and van Rossem et al. and the SPIRIT guidelines (23–25). Briefly, teams of medical students and surgical residents with senior staff surgeon oversight collect data on patients across Italy for 18 months. The Data Coordination Center (DCC) is the Colorectal Surgery Unit of Surgery Centre, – Fondazione Campus Bio-Medico University Hospital, University Campus Bio-Medico of Rome, Italy and the Study Director is responsible for the selection of the study sites. Any center performing emergency surgery can participate in this trial. The centers include academic medical centers, teaching hospitals, tertiary referral centers and community hospitals. Although this study protocol is similar to what adopted in previous research (26), in order to ensure that there is a uniformity of data acquisition, centers which do not participated in such previous study performed a 3-month pilot study collecting data retrospectively. All the data taken refers to the time of access of the patient in the emergency room or in any case to the first data available before any procedure. Such data are not published, and are stored separately for possible further analyses. All patients are treated according to the local hospital protocol and receive routine care as standard therapy. Whenever possible, patients with intestinal obstruction are treated according to SICUT Delphi consensus statements (27). The duration of the recruitment phase of patients is expected to be 18 months. The main strength of this project is the multicenter, prospective, contemporary methodology, with independent validation of data. This will produce high quality data on the emergency procedures carried out for gastro-intestinal emergency and on outcomes throughout Italy from a wide range of hospital types. Limitations include the inability to assess the postoperative visits to the general practitioner. Moreover, a minority of patients may present to other hospitals with complications following surgery, or because they need medical assessment. Despite this, teams will try to document the number of patients that were readmitted to other facilities. Our study uses the standard 30-day follow-up period, as this is the international standard and allows comparison to other studies. However, complications which may occur after 90 days will be reported as completely as possible.

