### Data collection, validation, and management

In each participating hospital, one local investigator (usually a surgical resident/student) is responsible for data collection and for entering data into a password-protected electronic spreadsheet specifically constructed with predefined data fields. There are six categories, namely “patient demographics”, “comorbidities”, “clinicopathological data”, “surgical intervention”, “score”, and “follow-ups” (Table 1). Patient details will be recorded and anonymized using the code centre, an ID number and a unique alphanumeric code for any further integration. The anonymization procedure is provided by the enrolling centre. Patient data will be collected, if possible, on a daily basis; preoperative and intraoperative data will be processed after surgery, and the postoperative outcomes will be noted at the time of discharge and at the end of follow-ups. Data will be obtained from the electronic patient database, from admission charts, and operative reports, or directly from the surgeon who performed the operation when details were unclear or missing. Consent to participate in the study and to collect data for scientific purpose will be obtained from the patient at admission. The standardized data collection protocol has been approved by the Central Ethical Committee. There is no minimum number of patients per centre. Following data collection, only datasets with >95% data completeness will be accepted for pooled national analysis. The principal investigator (PI) at the selected site will identify an independent assessor to validate all data, with a target of >98% accuracy. Overall, at least 5% of the datasets will be independently validated. Outcome data will not be analyzed specific to each individual center. Data will be submitted monthly *via* e-mail or inserted in an online module. Once in the Data Coordination Centre (DCC) pooled warehouse, records are reviewed and edited and, whenever necessary, transformed to comply with the GESEMM data dictionary (see Table 1 for further information). The Study Director and the Study Coordinator will then identify unacceptable data entries using custom software queries to detect missing, impossible and improbable values and logical inconsistencies between data fields and across the forms. The DCC will then ask the sites to check for the incomplete data, and once the sites have resolved the data queries, the DCC will update the patient records. To identify complications during follow-up, each center will check their database to monitor visits to the emergency department, postoperative imaging or intervention, outpatient visits or hospital readmissions. Additional checking of admission diagnosis and surgical procedures in the study months will identify any missing patients. The data will be collected from each individual center according to the current Italian Law regarding privacy policy (Legislative Decree no. 196/2003 “RIGHT TO PERSONAL DATA PROTECTION CODE”). It will be the responsibility of the local investigators to ensure that the local data will be protected and held according to such privacy policy and in line with what has been approved by the ethics board. No patients are involved in setting the research question or the outcome measures; nor are they involved in the design and implementation of the study. There are no plans to involve patients in dissemination of results.

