### Privacy

Data will be collected by each individual center anonymously according to the current privacy regulations (Annex/Art. 13 of Legislative Decree 196/2003 “CODE REGARDING THE PROTECTION OF PERSONAL DATA”), making use of a progressive identification number and a unique code for any patient. All data collection forms will be sent to a non-medical collaborator who will accumulate them in a single general database, ensuring the anonymity of the patients and the center that sent them. The data and their processing phase will be owned by the center promoting the Study, but at the disposal of the Principal Investigator of each center.

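### The named methods assume independent patients and nothing accounts for centre; intervals for the pooled rates and for centre-related predictors will be too narrow if outcomes cluster by hospital

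*Protocol article*

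**What the plan says.** The Statistical analysis section of the protocol article is specific about methods. It lists t tests, Mann–Whitney, Kruskal–Wallis and ANOVA, Fisher and chi-square tests with or without Yates correction, ROC analysis for each risk score, and correlation. For the multivariable work it says: "Multivariate analyses will be performed using logistic regression models that consider mortality and morbidity as dependent variables". It promises 95% confidence intervals where appropriate and sets the significance threshold at P<0.05. No section mentions clustering, a centre term, a mixed model, GEE or robust standard errors.

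Other sections describe how patients are grouped:

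- Study design and participating sites: "The centers include academic medical centers, teaching hospitals, tertiary referral centers and community hospitals". On treatment: "All patients are treated according to the local hospital protocol and receive routine care as standard therapy".
- Data collection, validation, and management: one local investigator per hospital enters the data, "There is no minimum number of patients per centre", and "only datasets with >95% data completeness will be accepted for pooled national analysis".
- The same section: "Outcome data will not be analyzed specific to each individual center". The Privacy section adds that the database is assembled "ensuring the anonymity of the patients and the center that sent them".
- Table 1 includes a numeric centre ID. It has no field for hospital type.

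**The concern.** The article itself gives three reasons to expect outcomes to be more alike within a hospital than between hospitals. Care follows local practice. Case mix should differ between a community hospital and a tertiary centre. Complications are found and entered locally, with complication type recorded as free text. Recorded 30-day morbidity, a primary outcome, could therefore vary with the recorder as well as with the patient.

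The primary results are pooled rates, and a pooled rate is the quantity most directly exposed to within-centre correlation. The Objectives also look for perioperative variables that predict adverse results and examine management strategies. Surgical approach and ICU admission can plausibly follow hospital habit, so a single-level model may credit them with differences that belong to the hospital. The one sentence about centre in the analysis, together with the promise of centre anonymity, could lead an analyst to leave centre out.

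**Working it through.** The article states no sample size, number of centres, centre size or ICC, so there is no figure of its own to reproduce. Every input below is an assumption and the results are shown as a range.

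**Interval for a pooled rate.** Let m be the mean number of patients per centre and CV the coefficient of variation of centre size.

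- Design effect: DE = 1 + [(1 + CV²)m − 1] × ICC, which is 1 + (m − 1) × ICC when centres are of equal size.
- Correct interval width relative to the naive one: √DE.
- True coverage of a nominal 95% interval: 2Φ(1.96/√DE) − 1.

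| ICC | m | CV | DE | Width ratio | True coverage |
|---|---|---|---|---|---|
| 0.005 | 20 | 0 | 1 + 19 × 0.005 = 1.095 | 1.05 | 93.9% |
| 0.01 | 50 | 0 | 1 + 49 × 0.01 = 1.49 | 1.22 | 89.2% |
| 0.02 | 50 | 0 | 1 + 49 × 0.02 = 1.98 | 1.41 | 83.6% |
| 0.02 | 50 | 0.8 | 1 + (1.64 × 50 − 1) × 0.02 = 2.62 | 1.62 | 77.4% |
| 0.05 | 100 | 0 | 1 + 99 × 0.05 = 5.95 | 2.44 | 57.8% |

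The third row in full: √1.98 = 1.407; 1.96/1.407 = 1.393; Φ(1.393) = 0.918; 2 × 0.918 − 1 = 0.836. The fourth row shows the cost of unequal centres, which the absence of a minimum per centre allows.

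**Logistic regression.** A simulation fitted ordinary single-covariate logistic models to data with a centre effect. It assumed 50 centres of 60 patients, a 10% event rate in an average centre, and 400 runs per setting. The ICC here is on the latent logistic scale, so it is not the ICC of the table above.

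| Latent ICC | Type I error, patient-level factor unrelated to centre | Type I error, centre-level factor | True/naive SE, centre-level factor | Odds ratio per SD, null factor correlated with centre effect |
|---|---|---|---|---|
| 0.01 | 0.030 | 0.100 | 1.16 | 1.04 |
| 0.02 | 0.068 | 0.095 | 1.19 | 1.06 |
| 0.05 | 0.055 | 0.170 | 1.43 | 1.09 |
| 0.10 | 0.050 | 0.280 | 1.80 | 1.13 |

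With 400 runs the Monte Carlo standard error around 0.05 is √(0.05 × 0.95/400) = 0.011, so the patient-level column is compatible with the nominal 5%. The centre-level column is not.

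The two calculations agree. A latent ICC of 0.05 at a 10% event rate is about (0.05/0.95) × 3.29 × 0.10 × 0.90 = 0.016 on the proportion scale. With m = 60, DE = 1 + 59 × 0.016 = 1.94 and √1.94 = 1.39, against a simulated ratio of 1.43.

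In the last column, the factor's centre mean was given a correlation of 0.7 with the centre effect and one tenth of its variance lay between centres. It shows what confounding by centre would do if present, not that it is present. The effect on AUC intervals was not computed, and the design effect for a rate need not carry over to them unchanged.

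**The case against.** The strongest objection is that this argues from silence. The article says only that logistic regression will be used. It lists no covariates and fixes no variance estimator, so it does not exclude a centre term, and a fuller protocol or analysis plan may specify one. A reader might infer that every test and model will treat patients as independent; the article does not say so. What remains is that the methods list is detailed, everything on it is single-level in standard form, and the only sentences about centre point away from using it.

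A reader might also infer that the rule on centre-specific analysis forbids adjustment for centre. Its natural meaning is that results will not be shown hospital by hospital, which fits the promise of anonymity, and a coded centre number can stay in the database. There is no contradiction, but the sentence needs clarifying.

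Other objections limit the scope:

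- Most Table 1 predictors are measured per patient, and those balanced across centres keep near-nominal error. Surgical approach and ICU admission can vary within a centre, so the full design effect would overstate their inflation.
- The inflated error rates in the centre-level column apply to purely centre-level factors. Hospital type is the obvious one, but no comparison by hospital type is planned.
- Centres are invited and selected, not sampled. If inference were confined to the participating hospitals, between-centre variation would not be sampling error. However, the article presents the study as nationwide and its outcomes as describing Italy.
- Senior oversight, a pilot at new centres, standard complication grading, independent validation and central queries should reduce recorder differences. They do not remove differences in care or case mix.

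**Conclusion.** The point holds in a limited form and should be corrected. If the named methods are used in standard form and the ICC is above zero, 95% intervals for the pooled 30-day morbidity and mortality rates will be too narrow, as will those for AUCs and for predictors that vary mainly between centres. With equal centre sizes, an ICC of 0.005 to 0.05 and 20 to 100 patients per centre, true coverage for a pooled rate runs from about 94%, which is negligible, to 58%. Unequal centre sizes lower it further. Since the article supplies none of these inputs, no single figure can be claimed.

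Two broader conclusions are tempting and not supported. One is that all confidence intervals are too narrow: those for patient-level predictors balanced across centres are about right. The other is that risk factors are confounded by centre: this requires both the factor and the outcome to differ by centre, and for management variables it is a plausible risk that has not been shown.

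**What to change.** Add the following to the Statistical analysis section, using the coded centre ID in Table 1:

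1. Report the primary rates and the AUCs with cluster-robust or centre-bootstrap 95% intervals.
2. Fit the logistic models for mortality and morbidity with a random intercept for centre, or use GEE or cluster-robust standard errors, and name the choice in advance.
3. For management variables such as surgical approach and ICU admission, add a sensitivity analysis with centre-mean terms or centre fixed effects. A plain random intercept assumes that the centre effect is unrelated to the covariates, so it does not by itself remove confounding by centre.
4. State that the rule on centre-specific analysis bars centre-by-centre reporting, and that neither it nor the anonymity promise bars adjustment for coded centre. This clarification is useful whatever a fuller plan contains.
5. Include hospital type as a covariate only if it can be derived from the centre ID, because it is not a listed field.

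The cost is wider intervals and slightly more analysis work. Items 1 to 4 need no new data, and both named software packages can fit the models.
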